
**Fig 1 pone.0347695.g001:**
[figure not shown]
Trial flow chart.

**Follow-up evaluations:** Data collection will commence on the day the participant is randomized into the trial and will continue until the trial is terminated or the participant withdraws from the trial at any time for any reason. Study visits will be scheduled every two weeks until 32 weeks and weekly thereafter until delivery [Table 1]. Participants will be monitored using a daily symptom diary to record features of severity—headaches, visual disturbances (e.g., blurred vision, scotoma), dyspnoea, and right hypochondria or epigastric pain and any adverse event—gastrointestinal upset, dry mouth, nausea, vomiting, diarrhoea, rash, and fatigue and its severity using a daily symptom diary and present this for recording at their next clinic visit. At every follow-up visit, a newly filled dispensing sachet containing the experimental drugs with the same numeric code will be given to each woman, and the pills remaining in used sachets are then counted to assess adherence. Adherence will be defined as the use of at least 70% of the prescribed tablets for each participant. Allocations to treatment arms will be concealed from the study investigators, clinic staff, and trial statistician using sealed opaque envelopes that are sequentially numbered. The onsite pharmacy technicians will not be involved in the design, conduct, statistical analysis, and reporting of study findings. Additional information to be collected during the follow-up visits includes a history of allergies, level of treatment adherence, drug tolerability, bedside urinalysis for albumin, venous blood samples for biweekly measurements of haemoglobin, creatinine, liver enzymes (AST/ALT), and complete blood count. Serum biochemical assessments of glutathione and homocysteine levels will be performed at randomisation (baseline) and at weeks 28 and 32. Fetal growth scans and umbilical artery velocimetry (from 32 weeks) will also be done biweekly until delivery. At delivery, data on gestational age (in weeks), total duration of experimental drug intake (in days), intrauterine growth restriction (IUGR), neonatal birth weight (in grams), neonatal status at birth, 7th- and 28th-day (dead/alive), neonatal intensive care unit (NICU) admission, and length of NICU admission (in days) will be collected and recorded in the electronic CRF. Cord blood sampling at delivery for analysis of glutathione and homocysteine levels will also be collected to provide additional insight into maternal-fetal antioxidant transfer and potential downstream effects of NAC [Table 1].

**Table 1 pone.0347695.t001:** Time and events schedule.

Study Phase	Screening	Treatment/Follow-up Phase (Gestational Age)^a^												
Week		24–34 weeks	25 weeks	26 weeks	27 weeks	28 weeks	39 weeks	30 weeks	31 weeks	32 weeks	33 weeks	34 weeks	Postpartum	End-of-Study^b^
Inclusion and exclusion criteria	X													
Informed consent (ICF)^c^	X	X												
Sociodemographic and clinical information	X	X												
Randomization		X												
Oral NAC/Placebo dispensing			X	X	X	X	X	X	X	X	X	X		
Compliance assessment^d^			X	X	X	X	X	X	X	X	X	X		
Follow-up evaluation visits				X	X	X	X	X	X	X	X	X	X	
Primary endpoint (preeclampsia with severe features)						X	X	X	X	X	X	X		
Secondary endpoints						X	X	X	X	X	X	X	X	
Assessment of serum glutathione and homocysteine						X				X			X	
CBC, Renal and Liver Function tests		X		X		X		X		X		X		
Fetal growth scans and umbilical artery velocimetry										X		X		
Postpartum outcomes (NICU admission, neonatal mortality)						X	X	X	X	X	X	X	X	X
Study close-out														X
Adverse event review^e^	Continuous review													

a. There will be a minimum of 1 week between routine follow-up visits during pregnancy.

b. End of study is defined as 4 weeks postpartum or in case of early dropout.

c. Informed consent must be signed before any study-related procedures.

d. Drug compliance will be assessed via pill count and self-report thereafter.

e. Adverse events and concomitant medications will be monitored throughout the study, from the signing of the ICF onwards, until the participant’s last study-related activity or until the participant has been deemed lost to follow-up after demonstrating due diligence in follow-up efforts.

### Management of adverse events

To ensure safety, participants will be educated on potential adverse events (AEs) such as gastrointestinal upset (nausea, vomiting, diarrhoea), rash, or rarely, allergic reactions and given 24/7 contact details of study staff. All AEs will be closely monitored at regular study visits using the symptom diaries to record any unusual symptoms or discomfort on each day, as well as between visits through scheduled check-in phone calls. Structured AE assessments will be conducted at each follow-up visit, and all AEs will be reported according to established standards [25]. Symptoms will be monitored without interruption of treatment unless bothersome to the participant. In the case of mild AEs, such as gastrointestinal upset, participants will be required to skip the next treatment dosage, and symptomatic treatment (e.g., antiemetics for nausea or vomiting) will be provided as appropriate. However, in case of persistent AE, the next treatment dosage will be delayed for 1 week and then completely discontinued if the AE persists. The PI may choose to discontinue a participant from the study for reasons such as serious AEs (SAEs), including significant renal or hepatic impairment or suspected unexpected serious adverse reaction (SUSAR), that is, a medical condition or situation in which continued participation in the study would not be in the best interest of the participant (codebreaking). Any SAE or SUSAR will trigger immediate clinical evaluation, and the event causing study discontinuation will then be documented in a dedicated CRF to capture the date and underlying reason for such discontinuation. Any participant experiencing an AE will be offered medical support, and our research insurance coverage will ensure that participants receive care at no cost as part of the study protocol. A Data and Safety Monitoring Committee (DSMC) will oversee safety evaluations throughout the study. The study will terminate if more than 30% of the enrolled patients experience SAE/SUSAR.

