### Study outcomes

The primary outcome measure was time-to-disease progression (in days) among women with early-onset preeclampsia, defined as the interval from diagnosis to the first occurrence of a composite endpoint indicating clinical deterioration. Disease progression is defined as the development of any of the following: consistently elevated blood pressure of 160/110 mmHg or higher; severe proteinuria of 3+ or a urine protein/creatinine ratio of 0.3 or higher; platelet counts less than 100,000/µL; elevated liver enzymes (AST/ALT) or evidence of hepatic dysfunction; serum creatinine level greater than 1.1 mg/dL or doubling of baseline creatinine in the absence of other renal diseases; symptoms and signs of pulmonary oedema such as dyspnoea and crackles on lung auscultation; cerebral or visual disturbances such as headaches, visual disturbances, altered mental status, seizures (eclampsia), or other neurological symptoms; and evidence of placental dysfunction such as placental abruption, fetal growth restriction or oligohydramnios on ultrasound examination [2,5]. Participants who do not experience disease progression will be censored at delivery or at the end of follow-up. Secondary outcomes will include (1) safety and treatment tolerability, (2) maternal outcome (maternal mortality), and (3) composite neonatal outcomes, including low birth weight in term neonates (baby’s birth weight less than 2500g), IUGR, stillbirth, NICU admission, and perinatal and neonatal mortality. Women who develop preeclampsia with severe features will be managed as per the obstetric unit protocol and will be excluded from further participation in the study.

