### Sample size calculation

The sample size was calculated assuming a 1:1 randomization ratio, a two-sided type I error rate (α) of 0.05, and 80% statistical power to detect a hazard ratio of 0.5 between the NAC and placebo groups, based on an estimated 33.3% baseline probability of disease progression among pregnant women with early-onset preeclampsia [24]. Allowing for an anticipated 15% loss to follow-up or missing outcome data, the total planned sample size is 153 participants, who will be randomly allocated in equal proportions to the two study arms (approximately 76–77 participants per group).

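### The pooled 30% SAE/SUSAR termination rule does not say whether disease progression counts, so the disease itself could stop the trial, while an excess in one arm could go unnoticed

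*Protocol article*

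**What the plan says.** Three parts of the protocol article bear on this point.

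- **Management of adverse events.** The rule is mandatory: "The study will terminate if more than 30% of the enrolled patients experience SAE/SUSAR". The denominator is everyone enrolled, so the arms are pooled. No relation to study drug is required, placebo is not used as a comparator, and endpoint events are not exempted. The grounds for discontinuing a participant are given as "serious AEs (SAEs), including significant renal or hepatic impairment", together with SUSARs. Any SAE or SUSAR leads to immediate clinical evaluation, and a DSMC oversees safety throughout.
- **Study outcomes.** Progression, the primary endpoint, is a composite. It includes "elevated liver enzymes (AST/ALT) or evidence of hepatic dysfunction" and "serum creatinine level greater than 1.1 mg/dL or doubling of baseline creatinine in the absence of other renal diseases". It also includes pulmonary oedema, eclampsia and placental abruption, and items that are not obviously serious events, such as 3+ proteinuria, headache and oligohydramnios.
- **Sample size calculation.** The trial is planned on "an estimated 33.3% baseline probability of disease progression among pregnant women with early-onset preeclampsia", a hazard ratio of 0.5, 80% power, two-sided 0.05, 1:1 allocation and 15% loss, giving 153 women.

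**The concern.** Renal and hepatic deterioration appear both as SAEs that feed a termination rule and as the disease outcome the trial is built to count. The protocol does not say how the two counts relate. If progressions are reported as SAEs, the threshold of 30% lies close to the rate of progression the trial expects, and an inert drug could be stopped because of the disease under study. If they are not, the rule behaves quite differently. Whether a mandatory termination takes effect therefore depends on a classification that the text leaves open.

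The opposite failure is also possible. A single percentage over both arms averages a harmful arm with a harmless one, so a real excess on NAC may not reach the threshold.

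**Working it through.** **Inputs.** From the protocol: threshold above 30% of enrolled women; N = 153 (77 and 76 by arm); baseline progression 33.3%; hazard ratio 0.5; two-sided 0.05; power 80%; loss 15%. Assumed, because it is not given: the share f of progressions that would be recorded as SAEs.

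**The plan's own N.** The events needed are 4(1.960 + 0.842)²/(ln 0.5)² = 65.3, so 66 (Schoenfeld), or 9(1.960 + 0.842)² = 70.6, so 71 (Freedman). Progression on NAC is 1 − (1 − 0.333)^0.5 = 18.3%, and the pooled rate is (33.3% + 18.3%)/2 = 25.8%. Dividing events by 0.258 and then by 0.85 gives 302 or 325, so 153 is not reproduced with 33.3% read as a progression probability. It is reproduced if 33.3% is the progression-free probability: the pooled rate is then 54.5%, and 70.6/0.545 = 130, 130/0.85 = 153. That is a separate matter. The main table uses 33.3% as written.

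**Trigger.** 0.30 × 153 = 45.9, so 46 women.

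**Chance that progression alone reaches 46 at full enrolment.** This is P(X₁ + X₂ ≥ 46), with X₁ ~ Bin(77, 0.333f) and X₂ ~ Bin(76, f·p₂). Under no effect p₂ = 0.333; at hazard ratio 0.5, p₂ = 0.183.

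| Share f counted as SAEs | No effect | HR 0.5 |
|---|---|---|
| 100% | 82% | 13% |
| 90% | 52% | 3% |
| 75% | 9% | 0.1% |
| 50% | about 0 | about 0 |

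**What moves these figures (f = 100%).**
- *Losses.* If the 15% lost have no recorded event, the rates are 0.85 × 33.3% = 28.3% and 0.85 × 25.8% = 21.9%. The chances fall to 34% and 1%.
- *Repeated checks.* The protocol gives no checking times. By simulation, checks at 77, 115 and 153 women give 88% and 25%. Checking after every woman from number 30 gives 95% and 54%. Both treat each outcome as known at enrolment, so they are upper-end illustrations.
- *Unrelated SAEs.* If a further 5% of women independently have one (assumption), the chances are 96% and 48%; at 10% they are 99.6% and 83%.
- *Event rate.* If progression were as frequent as N = 153 implies (66.7% and 42.3%), the HR 0.5 chance would be 24% at f = 50%, 79% at f = 60% and close to 100% at f = 100%.

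**Against the information target.** The design needs 66 to 71 events, which is 66/153 = 43% to 71/153 = 46% of the women. If all progressions count, the rule fires at 46 women, before that number can accrue. With 45 or 46 events, power at hazard ratio 0.5 is Φ(½√d · ln 2 − 1.960) = 64% or 65%. At the rates as written the trial expects only 77 × 0.333 + 76 × 0.183 = 39.6 events in any case, so the sample size also falls short of the target without the rule.

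**Sensitivity to a one-arm excess.** Assume SAE rates of 40% on NAC and 10% on placebo. The expected count is 77 × 0.40 + 76 × 0.10 = 38.4, and P(≥ 46) = 8%.

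**The case against.** The strongest objection is that nothing in the protocol makes every progression an SAE. Only renal and hepatic impairment are named, two of many components, and the table shows how quickly the risk falls once a quarter of progressions are left out. The symptom diary lists features of severity apart from adverse events, and women who progress leave the study by a route of their own, which hints at separate handling. This stands against any claim that the disease is likely to stop the trial. It does not remove the ambiguity, because no exemption is stated.

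A reader might also infer that the rule contradicts the planning figure because 33.3% exceeds 30%. The documents do not support that: 33.3% is the baseline rate, whereas the rule pools both arms, and the matching figure under the design effect is 25.8%.

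A reader might further infer that some 46 women could have unexpected serious reactions before anyone acts. That overlooks the immediate evaluation of each SAE or SUSAR, the provision for code-breaking, and DSMC oversight. Nor should NICU admissions be added to the count, since they concern the neonate and the rule counts enrolled patients.

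Finally, SAE definitions and by-arm review may well sit in the full protocol, SOPs or DSMC charter. Their absence from an article is no fault. The point here is the rule that the article does state.

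**Conclusion.** The concern holds in a limited form. A mandatory, pooled, cause-blind rule overlaps with the primary endpoint and is not reconciled with it. Followed as written, it can end the trial because of the disease. How probable that is depends on an unstated share: at full enrolment, from about 0 when half of progressions count to 82% under no effect, or 13% at hazard ratio 0.5, when all do. Those figures take the 33.3% as written and one check at the end, with no losses and no other SAEs. A chance above one half needs no drug effect and about 90% or more of progressions counted, or else repeated checks, additional SAEs or a higher event rate.

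The weak response to a one-arm excess does not depend on how progression is classified. Its 8% rests on assumed SAE rates, but dilution follows from any pooled count. The point should be settled before enrolment and rates as a change the sponsor should make.

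**What to change.** Reconcile the termination rule with the endpoint definition and the planning rate:

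1. State whether protocol-defined progression events count toward the 30% and, if so, which ones. Renal and hepatic impairment need explicit mention because they appear on both sides.
2. Keep maternal deaths and all other safety events under DSMC review whatever is decided in step 1. A blanket exemption for secondary outcomes would not do, because safety and maternal mortality are themselves secondary outcomes.
3. Have the DSMC assess SAEs by arm and not only as a pooled percentage.
4. Report SUSARs separately from the SAE percentage.

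The threshold and the list of events that count are for the sponsor and DSMC to set; none is proposed here. The cost is wording in the protocol and the DSMC charter, with no extra data. The article reports that recruitment had not begun at submission.

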### Plan to improve treatment compliance

Strategies to improve treatment compliance include (1) comprehensive education sessions to inform patients about the importance of adherence to the treatment protocol and the potential benefits of the experimental treatment; (2) use of automated reminders through phone calls, text messages, or emails to remind patients of their upcoming clinic visits and treatment schedules; (3) offering transportation support or reimbursement for travel expenses to study sites; (4) regular monitoring and check-ins by research staff to address any concerns or adverse events promptly and to reinforce the importance of adherence; (5) provision of small incentives, such as gift cards or other tokens of appreciation, to encourage adherence to treatment protocol.

### Plan to secure trial drugs and quality assurance

The study experimental drug (N-acetylcysteine) is currently available and approved by the National Agency for Food and Drug Administration and Control (NAFDAC) as an antidote for acetaminophen (paracetamol) overdose, helping to prevent or mitigate liver damage. We will establish a preliminary agreement with a reputable pharmaceutical company with extensive experience providing clinical trial materials in Nigeria to supply the study drug (NAC). We will follow a stringent procurement process, including verifying the credibility and compliance of suppliers with regulatory standards and ensuring proper documentation and certification for each batch of trial drugs. To maintain the highest quality standards, we will ensure that the trial drug is (1.) manufactured in facilities that comply with Good Manufacturing Practice (GMP) guidelines and (2.) stored under optimal conditions as specified by the manufacturers. Regular audits of storage facilities and periodic random sampling and trial drug testing will be conducted throughout the study to ensure ongoing quality and consistency.

### Participants’ recruitment and retention strategies

These include (1) implementing robust community engagement strategies to review study protocol by a participants panel and advocacy group and provide suggestions for ensuring that the study and recruitment approach is acceptable and feasible for patients; (2) developing clear, concise, and engaging messages that highlight the importance of the study and its potential benefits to participants and society; (3) utilizing community organizations, patient advocacy groups, and healthcare providers to reach potential participants; (4) using other recruitment sites, if necessary, to screen and enrol participants into the trial; (5) ensuring that study staff are trained in cultural competence and can communicate effectively with participants from different backgrounds; (6) ensuring participants and study staff feedback to improve recruitment efforts continuously; (7) printing and posting of sensitization posters and fliers within and around the recruitment clinics; (8) completion of the participant’s locator form for each enrolled woman and review at each follow-up visit to ensure that the participant’s contact information is up to date; (9) using of automated contact and scheduling of follow-up through short text message reminders; (10) assigning study staff to monitor scheduling and ensure participants tracking through personal phone calls 48 hours before or after (for failure to show) their scheduled follow-up visits; and (11) reimbursement of transportation cost and time spent during study-related visit at five thousand naira (₦5,000), equivalent to three US Dollars ($3.00), for each visit.

### Quality control and data monitoring

All investigators and research assistants will be required to undergo training, including Good Clinical Practice (GCP) training, prior to the trial to ensure consistent practice. The training will cover a comprehensive understanding of the inclusion/exclusion criteria, follow-up protocols, and questionnaire completion. The research assistant will transfer identifiable data to an electronic database system housed in a secure facility at the trial site. Access to identifiable data will be limited solely to the principal investigator ([name]) throughout and after the trial concludes. The trial will undergo monitoring by quality assurance personnel from the research management office of the College of Medicine, University of Lagos, who will operate independently from the study team. Regular monitoring will occur to ensure the accuracy and quality of data throughout the study duration. Monitors will oversee and verify the essential documents (consent information, enrolment records, protocol deviations, and instances of loss to follow-up) for accuracy and completeness. An independent data and safety monitoring committee (DSMC) will also review the interim analyses to ensure the robustness of the data, treatment safety, and adherence to the trial protocol.

### Data management and statistical considerations

Data will be collected prospectively with continuous data entry and checking. Queries will be actively pursued to ensure prompt clarification. Data will be entered into the REDCap database and then exported to Stata version 18.0 for Windows (StataCorp LLC, Texas, USA) for statistical analyses. Missing or incomplete data will be handled by running a missing values analysis using pairwise or listwise deletion if no pattern is detected or the multiple imputation method if a pattern is detected [26]. The primary analysis will be conducted on an intention-to-treat basis. The effectiveness of blinding will be evaluated using descriptive statistics and by comparing the proportion of correct guesses between study arms using the Chi-square test. Kaplan-Meier estimates with a Log-rank test will be used to calculate and compare the time-to-disease progression for the treatment groups while considering deliveries without preeclampsia with severe features as censored observations. We will then perform Cox proportional hazard models with a backwards conditional method to compare the study outcomes between the treatment arms while adjusting for other covariates using hazard ratios (HRs) and 95% confidence intervals (95%CIs). We will assess the calibration or goodness-of-fit statistic of the final model using the Hosmer-Lemeshow test, while the model’s explanatory power will be reported with Nagelkerke’s pseudo-R². Subgroup analyses will also be performed to assess the differential effects of significant covariates on the impact of NAC on disease progression. With oversight from the DSMC, two interim analyses of efficacy and futility for the primary outcome (progression to severe disease) will be conducted at 50% and 75% enrolment using O’Brien-Fleming stopping criteria [27] at cutoff *p*-values of less than 0.013 and 0.025, respectively

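### The missing-data rule deletes incomplete records when no pattern is detected, which does not fit intention-to-treat or the censoring rule and leaves women lost to follow-up without a defined treatment in the primary analysis

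*Protocol article*

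**What the plan says.** Three statements in the protocol article bear on a woman whose follow-up is incomplete.

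- **Data management and statistical considerations, missing data.** "Missing or incomplete data will be handled by running a missing values analysis", followed by "using pairwise or listwise deletion if no pattern is detected or the multiple imputation method if a pattern is detected". The rule covers everything missing or incomplete and does not exempt the primary endpoint. It does not say when deletion is pairwise and when listwise.
- **Same section, analysis set and censoring.** "The primary analysis will be conducted on an intention-to-treat basis". The Kaplan-Meier and log-rank analysis is described as "considering deliveries without preeclampsia with severe features as censored observations". Loss to follow-up is not named as a reason for censoring. The adjusted analysis uses "Cox proportional hazard models with a backwards conditional method".
- **Study outcomes.** "Participants who do not experience disease progression will be censored at delivery or at the end of follow-up". Footnote b of Table 1 also counts early dropout as end of study.

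Sample size calculation sets the expected scale: "Allowing for an anticipated 15% loss to follow-up or missing outcome data", with 153 women in total.

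**The concern.** Listwise deletion takes randomised women out of the analysis, and intention-to-treat is meant to prevent that. A time-to-event analysis has no need to do it, because a woman seen free of progression for some weeks contributes those weeks and is then censored.

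The trigger is also weak. The choice between deletion and imputation is made after looking at the data, and it treats failure to find a pattern as evidence that none exists. At this size a real difference in loss between arms will often go unnoticed. No check of observed data can show whether loss depends on the unobserved outcome. Such dependence is plausible here: Management of adverse events allows discontinuation for significant renal or hepatic impairment, which overlaps with components of the primary endpoint.

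At stake is bias in the treatment comparison, in a direction that cannot be known in advance. Two analysts who both follow the text could also analyse different sets of women.

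**Working it through.** **1. The 15% allowance.** 0.15 × 153 = 22.95, about 23 women, leaving 130. In reverse, 130/0.85 = 152.9, which rounds up to 153. The planned number already pays for these women as if they contributed nothing.

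**2. Chance that a check finds a real difference.** The article names no test, so a two-sided 5% between-arm comparison is assumed, with 76 women per arm and assumed loss of 10% v 20%.

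z = 0.10 / √(0.15 × 0.85 × 2/76) = 0.10/0.0579 = 1.73; power = Φ(1.73 − 1.96) = 0.41.

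In simulation, with the larger loss on NAC, detection was 26–47%. Some women progress before they would have been lost, so fewer than 23 are actually lost. With 5% v 25%, detection was 78–95%.

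**3. What deletion does to the hazard ratio.** A woman lost before progression has no observed event. Deleting her leaves the event count unchanged and removes her time at risk, which raises that arm's event rate. Suppose losses fall on average halfway through follow-up, and ignore the time cut short by events. The rate inflation in an arm with loss fraction q is then (1 − q/2)/(1 − q).

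| Loss in the two arms | Inflation in each arm | Ratio | True HR 0.50 becomes |
|---|---|---|---|
| 15% / 15% | 0.925/0.85 = 1.088 in both | 1.00 | 0.50 |
| 10% / 20% | 0.95/0.90 = 1.056; 0.90/0.80 = 1.125 | 1.066 | 0.53 if NAC loses more; 0.47 if placebo does |
| 5% / 25% | 0.975/0.95 = 1.026; 0.875/0.75 = 1.167 | 1.137 | 0.57 if NAC loses more; 0.44 if placebo does |

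**4. Simulation.** Log-rank test, 76 v 77 women, exponential event times, uniform dropout times, and control progression of 33.3% or 66.7%.

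- *Balanced 15%.* HR 0.51 with deletion, 0.50–0.51 with censoring. Power 52% v 53% (33.3% progression) or 85% v 86% (66.7%). Type I error about 5% both ways. Observed events are identical (36.7 and 36.7; 77.9 and 77.9).
- *10% v 20%.* Deletion gives HR 0.53–0.54 with the larger loss on NAC and 0.47–0.48 with it on placebo. With the larger loss on NAC, power falls by 7–9 points against censoring and type I error is 5.5–6%. Among only those trials where the check finds nothing, so that deletion applies, HR is 0.53–0.54 against 0.51–0.52 with censoring.
- *5% v 25%.* HR about 0.57–0.58 or 0.44, type I error about 7–9%.

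**5. Covariates in the Cox model.** Here deletion can remove women who had events. The article gives neither a covariate count nor a missingness rate, so these are assumptions, with values missing independently: ten covariates each 3% missing lose 1 − 0.97^10 = 26% (about 40 of 153); five each 3% missing lose 1 − 0.97^5 = 14% (about 22); ten each 1% missing lose 1 − 0.99^10 = 10% (about 15).

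For power at HR 0.5, use Φ(½√D × ln 2 − 1.96), where D is the number of events. Starting from 130 women, a further 5–15% deletion takes power from 83% (D = 70.8) to 81–77% if 66.7% of controls progress, or from 52% (D = 33.6) to 50–46% if 33.3% do.

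**The case against.** The strongest defence is that Study outcomes already does the right thing. Censoring at the end of follow-up, with early dropout counted as end of study in Table 1, naturally keeps a lost woman up to her last contact. The log-rank test needs only arm, time and status, so a missing covariate removes nobody from it. This stands as far as it goes: the article does not say that follow-up time will be thrown away. But the analysis section names only deliveries as censored and gives a deletion rule with no exemption, so the two sections still need reconciling.

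A reader might infer that deletion costs the trial events and power in proportion to the 15%. The documents do not support that. Women lost before progression have no observed events to delete, balanced loss costs about one point of power, and the 15% is already in the 153. A reader might also infer that deletion is the default. The rule has two branches, and neither is called the default.

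The loss splits by arm are assumptions, and under the more extreme one a check would usually find the imbalance and send the analysis to imputation. That is fair, and it limits the claim to moderate differences in loss. It is also true that if women leave because they are worsening, censoring at the last assessment is itself informative. Censoring removes the distortion that deletion adds, but only a sensitivity analysis addresses the rest.

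Finally, the contents of an imputation model belong in a statistical analysis plan, and their absence here is no fault. The deletion rule, however, is stated in the article and is stated badly.

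**Conclusion.** The point holds as a badly fixed rule and an unresolved conflict between two sections. Deletion conditional on finding no pattern does not fit the intention-to-treat commitment, and the article does not settle whether a woman lost to follow-up is censored or deleted.

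The harm is possible bias. It is modest under an assumed 10% v 20% loss and larger under 5% v 25%. It can dilute the effect or exaggerate it. It is close to nil if loss is balanced between arms and independent of outcome. These sizes rest on assumed loss splits, exponential event times and uniform dropout times, none of which the article gives. Loss of observed events arises only from dropping women with missing covariates from the adjusted Cox model, and its extent depends on covariate numbers and missingness rates that the article does not state.

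**What to change.** 1. Remove the rule that chooses deletion or imputation from a pattern check, including the open choice between pairwise and listwise.
2. State in Data management and statistical considerations that all randomised women are in the primary analysis, and that those lost are censored at their last assessment free of progression, in agreement with Study outcomes.
3. Use multiple imputation under missing at random by default for missing baseline covariates and secondary outcomes. The imputation model can be set out in the statistical analysis plan.
4. Add a prespecified sensitivity analysis for loss related to progression, for example a delta adjustment, because censoring at the last assessment may itself be informative.

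The cost is rewording and modest extra programming. No new data are needed, and Trial status says recruitment had not begun at submission, so the change can be made before any outcome is seen.
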